The sample size was calculated based on the primary outcome measures (potentially modifiable risk factors for falls, especially motor risk factors). The sample size was calculated using the statistical program G*Power 3.1, assuming (1) the purpose of identifying the effectiveness of risk factors after 16 weeks of intervention; (2) the test used (two-way ANOVA, considering group and time effects, with Bonferroni test to control type I error due to multiple primary outcomes); (3) the main measure; (4) type I error at 5%; (5) statistical power at 80%; and (6) an effect size of 0.25, a minimum of 28 people should constitute the total sample. Furthermore, to verify the sociodemographic and clinical factors that influence adherence and satisfaction, the rule of at least 10 cases of the outcome (success or failure, depending on which is rarer) was used for each independent variable used in the logistic/linear regression model [12]. Thus, considering an adherence of 80% based on a previous study by the research group [9] and the use of univariate regression analyses, a minimum of 50 people should constitute the total sample. With the chance of losing 20% of participants, a sample of 60 people in total is estimated.

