To verify the effectiveness of the interventions, the chi-square association test will be used for categorical variables. About the use of fNIRS, a pilot study was conducted before data collection, and the fNIRS signal demonstrated good quality across the targeted channels and participants, with minimal signal loss or saturation. This assured us the feasibility and reliability of the measurements. Regarding the data workflow, motion artifact control, and ROI selection, at this stage, the specific fNIRS data analysis is still ongoing, and a preregistered analysis plan has not yet been developed. We intend to finish this step until the end of 2025. Using the fNIRS, the digitizer data will be entered into the NIRS-SPM software package (v. 4), implemented in MATLAB 2017 (Natick, MA, USA). The fNIRS data will be preprocessed using custom MATLAB algorithms [51]. For quantitative variables, the two-way ANOVA test will be used to verify the interaction between groups and evaluations, with Bonferroni test to control type I error due to multiple primary outcomes. If an interaction is identified, simple main effects analyses will be performed, with adjustments for multiple comparisons (Bonferroni). To verify the proportion of individuals who did not suffer any fall episode during the 12-month follow-up (“proportion of people who did not have the first fall” and “proportion of people who did not have the second fall”), the Kaplan–Meier analysis will be used.

To verify adherence and satisfaction with interventions and sociodemographic and clinical factors that influence them, descriptive analyses of quantitative and qualitative data will be used, using the MAXQDA2022 software for coding and categorization. The excerpts of the responses will be separated into segments containing the ID of each volunteer and their corresponding code. After coding, the segments obtained will be organized using Bardin’s content analysis [52]. Furthermore, simple linear regression analysis will be used to verify possible influences of adherence (frequency) and satisfaction (score). Also, descriptive analyses and the chi-square association test will be used.

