To address missing data resulting from loss to follow-up, we plan to use multiple imputation methods under the assumption of missing at random and to perform sensitivity analyses using mixed-effects models, which can accommodate unbalanced data and account for intra-individual variability over time. These approaches will help to minimize potential bias associated with missing outcome data.

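### The stated aim is the 16-week effect, but the between-arm comparison is conditional on a group-by-evaluation ANOVA interaction without baseline adjustment: valid, but inefficient

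*Protocol article*

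**What the plan says.** **Aim and size (protocol article, section 2.3).** The first listed assumption of the primary-outcome calculation is "the purpose of identifying the effectiveness of risk factors after 16 weeks of intervention". The test is "the test used (two-way ANOVA, considering group and time effects, with Bonferroni test to control type I error due to multiple primary outcomes"), with "type I error at 5"% and "statistical power at 80"%. The result is "an effect size of 0.25, a minimum of 28 people should constitute the total sample". A separate rule for the adherence and satisfaction regressions then gives "a minimum of 50 people should constitute the total sample", which is raised to 60 for a 20% loss.

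**Visits (section 2.5).** There are four assessments: baseline, 16 weeks, 6-month follow-up and 12-month follow-up.

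**Analysis (section 2.9).** Quantitative outcomes are analysed by two-way ANOVA for the interaction between groups and evaluations, with Bonferroni across the primary outcomes. What follows is conditional: "If an interaction is identified, simple main effects analyses will be performed, with adjustments for multiple comparisons (Bonferroni"). No baseline covariate and no single primary time point is named.

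**Missing data (section 2.9).** Multiple imputation under missing at random (MAR) is planned. The authors also intend "to perform sensitivity analyses using mixed-effects models, which can accommodate unbalanced data".

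**The concern.** The question named in section 2.3 is a between-arm comparison at one time. The test in section 2.9 asks whether the arms differ in their pattern over all evaluations, and the 16-week comparison is reached only if that broader test is significant. Supervised exercise and weekly case-management contact stop at week 16 (sections 2.4.1 and 2.4.2), and the Discussion itself notes that adherence declines over time. A 16-week effect that partly fades is therefore plausible, and that is the pattern in which the interaction test is weak.

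Baseline is measured before treatment and should correlate with later values. Treating it as one more outcome visit uses that correlation less well than treating it as a covariate. In a trial of 60 the lost precision is worth recovering.

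On missing data, a likelihood-based mixed model is valid under the same MAR assumption as the imputation. Agreement between the two says nothing about dropout driven by unobserved decline, which is credible in older people selected for high fall risk.

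**Working it through.** **1. The plan's own figure.** For a within-between interaction with two groups, m measurements and correlation r: λ = f²·N·m/(1−r), with df m−1 and (N−2)(m−1). Take f = 0.25, alpha 0.05 and power 80%. The article states neither m nor r. At r = 0.5 the smallest even N is 34 for m = 2, 28 for m = 3 and 24 for m = 4. For m = 3, λ = 0.0625×28×3/0.5 = 10.5 and power is 0.81. N = 28 also results from m = 2 with r = 0.6. So 28 is reproducible, but it does not settle which visits the ANOVA is meant to include.

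**2. Inputs for the comparison.**
- From the article: 60×0.8 = 48 completers, 1:1 allocation, four visits, alpha 0.05.
- Assumed: 16-week difference d = 0.7 SD; r = 0.5 (range 0.3 to 0.7); equal correlation between all visits; unit SD; no Bonferroni correction; all four visits in the ANOVA.

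**3. Formulas.**
- Interaction: λ = (N/4)·Σ(d_t − mean d)²/(1−r), with df 3 and 138 (critical F 2.67).
- Two-visit change test: the same formula with two visits, df 1 and 46.
- Baseline-adjusted 16-week contrast: noncentrality d·√N/(2·√(1−r²)), 45 df.

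**4. Numbers at d = 0.7, r = 0.5.**
- Sustained (0, 0.7, 0.7, 0.7) or 16-week only (0, 0.7, 0, 0): the sum of squares is 0.75×0.49 = 0.3675 in both; λ = 12×0.3675/0.5 = 8.82.
- Partial fade (0, 0.7, 0.35, 0.175): 0.547×0.49 = 0.268; λ = 6.43.
- Growing (0, 0.7, 0.875, 1.05): 1.297×0.49 = 0.635; λ = 15.25.
- Two visits: 0.5×0.49 = 0.245; λ = 5.88.
- Baseline-adjusted: 0.7×6.93/(2×0.866) = 2.80.

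| Power, d = 0.7, 48 completers | r = 0.3 | r = 0.5 | r = 0.7 |
|---|---|---|---|
| Interaction, sustained or 16-week only | 0.53 | 0.69 | 0.90 |
| Interaction, partial fade | 0.40 | 0.54 | 0.78 |
| Interaction, growing effect | 0.79 | 0.91 | 0.99 |
| Two-visit change test | 0.52 | 0.66 | 0.87 |
| Baseline-adjusted, 16 weeks | 0.70 | 0.78 | 0.91 |

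**5. Where the loss arises.** At r = 0.5, baseline adjustment takes the two-visit test from 0.66 to 0.78. The variance ratio to change scores is (1−r²)/(2(1−r)) = 0.75, a 25% reduction. Moving from two visits to the four-visit interaction costs nothing if the effect is sustained or confined to 16 weeks (0.69 against 0.66). Under partial fading it costs about a further 12 points (0.66 to 0.54).

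**6. At the planned effect.** With two visits f = d/4, so f = 0.25 means d = 1.0. At r = 0.5 the interaction has 0.95 (sustained) or 0.86 (partial fade), against 0.97 baseline-adjusted. With Bonferroni over 16 outcomes (assumed, one per row of Table 1) these become 0.75, 0.54 and 0.80.

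**The case against.** **The test is the same in both sections, and four visits is an inference.** Both name a two-way ANOVA, and section 2.9 does not number the evaluations. With baseline and 16 weeks only, the interaction would itself be the 16-week change contrast and the precondition would be harmless. This stands as a caveat: four visits is the natural reading of sections 2.5 and 2.9, not a stated fact. The missing baseline adjustment would remain either way.

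**The fading pattern is a chosen one.** Half then a quarter gives a sum of squares of 0.547d², close to the minimum possible of 0.50d². Complete disappearance after 16 weeks gives 0.75d², the same as a sustained effect. The article does not predict fading: the intervention arm also receives a guidance manual and is encouraged to keep to the agreed recommendations. This stands, and a growing effect would favour the interaction test.

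**Baseline is not ignored.** It enters as the first evaluation, so the interaction measures differential change. This is correct; the issue is efficiency.

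**The size depends on unstated inputs.** d and r are not in the article, and 48 completers sets aside the planned intention-to-treat analysis with imputation. This also stands; the table therefore shows a range.

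**Missing data.** Section 2.9 does not claim that the mixed model tests departures from MAR, and such an analysis may sit in a plan not shown. That makes this point secondary, though the shared assumption is a fact.

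**Conclusion.** The point holds as one of efficiency. The plan aims at 16 weeks but makes the between-arm comparison conditional on a broader interaction, and it does not adjust for baseline. Under the assumptions above, the baseline-adjusted contrast gains about 9 points for a sustained or 16-week-only effect at r = 0.5 and about 25 points under partial fading. For a sustained effect the gain is about 17 points at r = 0.3 and about 1 point at r = 0.7. Missing baseline adjustment explains the loss unless the effect fades partially; then the interaction precondition adds about as much again.

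A reader might infer three stronger things that the article does not support:
- **That the trial of 60 is sized on the 16-week effect.** That calculation gives 28; the 60 comes from the adherence rule of 50 plus loss.
- **That the analysis is invalid or leaves the trial below 80% power.** It is valid, and at d = 1.0, r = 0.5 with uncorrected alpha the interaction keeps 0.86 or more. A shortfall appears only with a smaller effect, with lower correlation combined with fading, or after correction for many outcomes.
- **That a four-visit interaction wastes power in itself.** It does so only under partial fading.

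**What to change.** In section 2.9, make the primary analysis of the quantitative outcomes a linear mixed model for repeated measures, which the article already plans as a sensitivity analysis:
- follow-up visits as outcomes;
- baseline value as covariate, by visit;
- terms for arm, visit and arm-by-visit, with unstructured covariance.

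Name the arm contrast at 16 weeks as the primary test, not conditional on an interaction. Keep the Bonferroni correction across primary outcomes. Make the 6- and 12-month contrasts secondary.

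As the secondary change, add one delta-adjusted or control-based multiple imputation analysis, so that the sensitivity analysis departs from MAR.

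The cost is wording and a little more modelling; no participants, visits or measurements are added. What is given up is the omnibus test, which would be the more powerful if the effect grew after 16 weeks.

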## 3. Discussion

Older adults’ adherence to interventions declines over time, presenting a challenge in achieving sufficient participation, adherence, and persistence in both routine health and social care services [53,54]. Factors such as psychological, cognitive, behavioral, physical, or organizational aspects can influence adherence to a program [55]. Therefore, we believe that case management providing follow-up visits can improve adherence to the program by encouraging confidence by giving older adults an active role and contributing to the success of the present programs for preventing falls [56,57].

The multicomponent physical exercise program is the recommended strategy for improving most, if not all, of the hallmarks of frailty syndrome, including the incidence of falls, poor balance, reduced muscle strength, and poor gait ability. However, it is important to include gradual increases in the volume, intensity, and complexity of the physical exercises in the individual protocol [58]. Due to the need to individualize the program and monitor risk factors, case management is a fundamental care strategy.

Since we intend to reach a larger sample in this program and use challenging tools and protocols, it will be carried out in a hybrid format. We recognize that we may have difficulties moving volunteers to carry out the assessments and part of the training protocol. This factor can be solved by offering travel arrangements for participants to the research center. Furthermore, because this project involves case management, and that brings the volunteers closer to the work team, this factor can be minimized. A previous study showed good treatment credibility based on case management, as well as good adherence to their commendations [9].

Previous studies have reported positive results of case management interventions in reducing risk factors for falls and improving adherence among older adults [5,6,9,10]. For example, Sossai et al. (2024) demonstrated that a case management strategy significantly reduced the incidence of falls in older adults with a history of recurrent falls [6]. Similarly, Janducci et al. (2023) found high levels of treatment fidelity and satisfaction with case management recommendations in community-dwelling older adults [9]. However, these studies had limited scope regarding long-term follow-up and implementation in primary health care settings. Our protocol advances this field by combining the case management intervention with a structured physical exercise program and assessing its feasibility in the Brazilian public health context. The expected results may provide additional evidence to support the integration of these interventions into routine care for older adults at high risk of falls.

Despite the excellent results obtained in the application of the previous protocol [8], we sought, in this second version, to improve the clinical trial. With regard to proximity to the public network: previous studies have concluded that case management is effective for individuals with complex conditions, improving their clinical outcomes and reducing costs for other health sectors [59,60]. Especially in Brazil, the implementation of case management programs in primary care, the gateway for older people to health services, has become an important care strategy [4].

In this second version, we will apply the protocol to older people at high risk of falls, in accordance with the last Worldwide Guideline [3]. The most recent recommendations will be applied, especially with regard to the creation of a case management protocol centered on the older person, including their perspectives and those of their caregivers and family members, following the classifications of falls, their risk stratification, physical exercises, medications in use, multi-domain and multi-component interventions, and telehealth and smart home systems [3].

Another important improvement will be that the assessments will be in-person and not remote, as in the previous protocol the monitoring took place during the COVID-19 pandemic. Furthermore, we hope to identify the minimum clinically relevant difference in tests that assess neuropsychological risk factors for falls and understand the adherence and long-term satisfaction of older people in the intervention.

Since randomized clinical trials are considered the gold standard for evaluating the effectiveness of interventions due to their ability to minimize bias and establish causal relationships between interventions and outcomes, our methodological choice was based on this fact to provide high-level evidence on the effectiveness of our interventions for preventing falls in older adults. In addition, block randomization ensures a balance between groups, and blinding of evaluators reduces detection bias, making the results more robust. Finally, the fact that we conducted the intervention in the primary health care context will allow us to assess not only the effectiveness of the intervention but also the potential implementation challenges that may arise throughout the project, which is extremely important for future implementation of public health strategies.

This study has some limitations that should be considered. For example, the recruitment strategy may favor volunteers who are more motivated or have better access to health services, introducing a potential selection bias. Furthermore, because the intervention involves multiple locations and coordination between different municipalities, logistical challenges, such as participant retention and intervention fidelity, may pose obstacles throughout the study’s development. To this end, the negotiating meetings with the municipalities enabled a more secure alliance between the partners. Despite these limitations, the rigorous design, evaluator blinding, and justification strengthen the study’s internal validity.

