## 2. Materials and Methods

### 2.1. Trial Design

The MAGIC (v. 2) trial is a randomized, controlled, assessor-blinded, single-center (one main research center with collaborators from other centers, with an expectation to cover at least 8 different health territories) superiority trial with two parallel groups. The randomization will be performed as block randomization (random sizes) with a 1:1 allocation (Figure 1).

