### 2.3. Recruitment and Participants

Screening will continue until the target population is achieved. The subjects will be recruited by telephone contact during business hours among eligible individuals and individuals treated at primary to tertiary health units, social and educational services, and from the research group’s database and some community groups. In addition, there will be dissemination through pamphlets, posters, radio and television channels, and social networks, with the assistance of the UFSCar’s communication team. The enrollment period will extend over 9 months.

The volunteers will provide written, informed consent before any study procedures occur. People eligible for the trial will be aged ≥60 years old, resident in the Araraquara DRS (Coração region), non-institutionalized, with a history of at least one fall in the last year, and possibility of contact by telephone. Inclusion criteria will be a level of consciousness that allows the volunteer to be an active subject in the intervention; high falls risk according to the Worldwide Guideline for falls prevention and management for older adults [3], i.e., older adults with a history of at least 1 fall in the last year and one or more of the following characteristics: (i) injurious fall, (ii) multiple falls (≥2 falls) in the last year, (iii) presence of frailty syndrome, (iv) inability to get up after a fall without help for at least one hour, and (v) fall accompanied by (suspected) transient loss of consciousness; ability to walk alone with or without a walking aid; and willingness to participate in the proposed assessments and interventions.

Exclusion criteria will be as follows: a severe and uncorrected hearing and visual impairment that hinders communication during the intervention; neurological diseases that rapidly modify falls risk, including multiple sclerosis, diagnosis of moderate to advanced dementia, epilepsy, and traumatic brain injury, or taking associated medications; and contraindication to physical exercise (acute infectious disease, dissecting aortic aneurysm, severe aortic stenosis, congestive heart failure/unstable angina, acute myocardial infarction, acute myocarditis, acute pulmonary or systemic embolism, thrombophlebitis, ventricular tachycardia, and other dangerous arrhythmias) (Figure 2).

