### 2.4. Interventions

#### 2.4.1. Control Group

The Control Group and the Intervention Group will perform the physical exercise protocol for 16 weeks (twice a week) in Health Units, in partnership with trained physiotherapists and physical educators from primary health care and the assistance of the research team. The program will consist of a 10 min warm-up, 20 min balance and gait physical exercises, including how to get up after a fall, 20 min muscle strength physical exercises for the trunk and lower limbs with a functional focus, and 10 min cool-down (muscle stretching and breathing physical exercises), totaling 60 min per session and 120 min per week [13,14]. The physical exercises will have moderate intensity and individualized progression every 3 weeks. Moreover, the participants from the Control Group will be encouraged to maintain their routine and will receive monthly telephone calls for general health guidance.

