### 2.8. Randomization and Blinding

Participants will be randomly assigned to the Intervention or Control group with a 1:1 allocation using computer-generated randomization software with blocks of random sizes (2, 4, 6). All allocation concealment mechanisms will be conducted by other independent researchers. An independent researcher will open sequentially numbered, opaque, sealed containers with printed randomization numbers and the corresponding group. The researcher then will give information about treatment allocation to the volunteer and care manager staff.

Assessments will be conducted by trained assessors blind to treatment allocation. Due to the nature of the intervention, neither participants nor care managers can be blinded to allocation. They are strongly oriented not to disclose the allocation status of the participant during assessments. The blinded researchers will not have access to information about the allocation until the assessment ends (Figure 4).

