### 2.9. Statistical Analysis

A descriptive analysis will be performed. A significance level of α = 0.05 will be adopted for all analyses and the SPSS (22.0) software will be used to perform the statistical tests. The analysis will be performed by intention to treat. The Kolmogorov–Smirnov normality test will be applied to all continuous variables to verify data distribution. To compare groups regarding clinical and sociodemographic characteristics, the chi-square association test for categorical variables, the independent *t*-test for continuous variables with normal distribution, and the Mann–Whitney test for continuous variables with non-normal distribution will be used.

If the normality hypothesis is rejected, the z-score calculation will be performed to standardize continuous data. Volunteers will be classified as having no clinical improvement when the GRCS score is between −7 and 0, moderate improvement between 1 and 3, and great improvement between 4 and 7 after the intervention. The anchoring technique will be used to estimate the minimum clinically relevant difference, using the GRCS as an anchor. Correlations between the GRCS and performance changes of each test will be conducted. The Receiver Operating Characteristic (ROC) analysis will be used to compare the values of each test between volunteers who improved and did not improve according to the GRCS. Through this method, the cutoff score, specificity, and sensitivity of each test will be analyzed [15].

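### Unstratified blocks balance arm sizes only, so the Discussion's claim of balance does not extend to prognosis; the falls comparison should account for prior-year falls

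*Protocol article*

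**What the plan says.** Section 2.1 of the protocol article describes "block randomization (random sizes) with a 1:1 allocation". Section 2.8 gives the block sizes as 2, 4 and 6. Neither section names a stratification factor. Section 2.3 sets the size: "a sample of 60 people in total is estimated", which is 30 per arm.

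The Discussion then states that "block randomization ensures a balance between groups" and presents this, together with assessor blinding, as making the results more robust.

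Falls are among the primary outcomes (section 2.6). Eligibility (section 2.3) requires at least one fall in the last year plus at least one further feature, of which "multiple falls (≥2 falls) in the last year" is only one. The sample will therefore mix people with one prior fall and people with several, and the count is known before allocation.

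For falls over the 12 months, section 2.9 names a Kaplan–Meier analysis of first and second falls. It names chi-square tests for categorical variables and a group-by-evaluation ANOVA for quantitative ones. None of these is described with a covariate.

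**The concern.** Permuted blocks constrain how many people go to each arm. They do not constrain who those people are. Without strata, the share of recurrent fallers in each arm is left to chance, as it would be under simple randomization. Read as a statement about comparability of the arms, the Discussion sentence credits the design with a property it lacks.

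At 30 per arm this matters in practice. Falling repeatedly in the past year plausibly predicts falling again, and falls are a primary outcome. If the arms happen to differ in this respect, an analysis that ignores it yields an estimate partly shaped by the accident of allocation. Even when the arms are even, it leaves variation in the comparison that a variable already collected could explain.

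**Working it through.** **Size of the trial.** Section 2.3 uses 10 cases of the rarer outcome per regression variable with 80% adherence, so 10 / 0.20 = 50. Adding 20% gives 50 × 1.2 = 60, the stated total. At 1:1 this is 30 per arm.

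**What the blocks do control.** In 20,000 simulated allocations of 60 people with blocks of 2, 4 and 6 (equally likely, no strata), arm sizes never differed by more than 2 and were equal in about 81% of runs. Balance of head counts is real.

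**What they do not control.** Prevalence of recurrent falling is not given in the article, so it is an assumption. Let X and Y be the numbers of recurrent fallers in the two arms of 30. A gap of 20 points is |X − Y| ≥ 6.

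- *Prevalence 50%, number of carriers varies by sampling.* X + (30 − Y) is binomial (60, 0.5), so P = 2 × P(B ≤ 24) = 0.155. Simulation with the actual block scheme gives 0.147 to 0.148.
- *Exactly 30 of 60 are carriers.* X is hypergeometric (60, 30, 30), and P = P(X ≤ 12) + P(X ≥ 18) = 0.196.
- *Exactly 18 of 60 (30%) are carriers.* P = P(X ≤ 6) + P(X ≥ 12) = 0.158.

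The answer is therefore about 15 to 20%. The two 50% figures differ because, with 30 carriers fixed, the gap can move only in steps of 2/30.

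**What such a gap would do to one estimate.** Suppose recurrent fallers fall at k times the rate of single fallers (k is assumed) and the split is 60% versus 40%, with no treatment effect. The rate ratio is (0.6k + 0.4) / (0.4k + 0.6):

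| k | Calculation | Rate ratio |
|---|---|---|
| 1.5 | 1.3 / 1.2 | 1.08 |
| 2 | 1.6 / 1.4 | 1.14 |
| 3 | 2.2 / 1.8 | 1.22 |

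These values are conditional on a gap of that size, and the gap is equally likely to favour either arm.

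**Long-run error rate.** With N = 60, the same blocks, 50% recurrent fallers at three times the rate and no treatment effect, the unadjusted log-rank test rejected in 5.3% of 4,000 simulated trials. The nominal level is kept.

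**What adjustment gains.** Taking prior falls (one versus two or more) into account raised simulated power from 57% to 61% at k = 2 and from 61% to 68% at k = 3, with type I error still near 5%. The gain is 4 and 7 points. It also rests on an assumed fall rate and treatment effect. I repeated the exercise with other assumed values: the gain at k = 2 was a few points or less, and at k = 3 it was clearer. The direction is firmer than the exact size.

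**What stratified blocks would do.** With two strata by prior falls (30/30 or 18/42), a gap of 10 points or more did not occur in 20,000 runs. The 95th percentile of the gap was 3 to 5 points, and arm totals differed by 4 or more in under 2% of runs.

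**The case against.** **The sentence may mean only group sizes.** It does not mention prognosis, and blocking does balance numbers. No design or analysis step relies on the wider reading. That is fair, and it keeps the wording point small. Still, the sentence is offered as a reason for robust results, and equal head counts alone give little support for that.

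**A condensed article may leave strata and covariates to a full protocol or analysis plan.** This also stands. Their absence here does not show that they are missing from the trial. What can be said is that the Discussion claim is too wide for the design described, and that the falls analysis as stated can be improved.

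**A reader might infer that chance imbalance biases the falls result or produces false positives.** The design does not support that. Chance imbalance is part of the random error that p-values and intervals already cover, as the 5.3% rejection rate shows.

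**A reader might extend the point to Health Units**, since exercise is given "in Health Units, in partnership with trained physiotherapists and physical educators from primary health care" and the trial is planned "with an expectation to cover at least 8 different health territories". With 8 equal territories, at least one would have 75% or more of its people in one arm in 78% of simulated trials. But these are cells of 7 or 8 people, both arms exercise in Health Units, and stable unit differences in level largely drop out of a group-by-evaluation interaction test if it is run as repeated measures. No between-unit variation is given from which to size a loss. Fixed unit effects would need 8 − 1 = 7 parameters. With arm and prior falls that makes 9, or about 90 events under the article's own 10-per-variable rule, from 60 people. A demand for unit in every model is not justified.

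**Baseline significance tests** ("To compare groups regarding clinical and sociodemographic characteristics, the chi-square association test for categorical variables") are a matter of reporting style and change no treatment comparison.

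**Conclusion.** The point holds in a limited form. Unstratified blocks of 2, 4 and 6 balance arm sizes, not prognosis. With 30 per arm, a 20-point gap in a factor such as recurrent falling arises in about 15 to 20% of trials at 50% prevalence, and about 16% at 30%. The cost is precision and the trust that one small estimate deserves, not bias on average or an inflated error rate. Adjusting for prior falls is a better method than the unadjusted falls analysis stated, with a modest gain: about 4 to 7 points of power if recurrent fallers fall at two to three times the rate of single fallers.

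The prevalence, the rate multiple, and the fall rate and treatment effect behind the power figures are assumptions. Sixty is described as a minimum; a larger sample would make large gaps less likely.

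**What to change.** 1. In section 2.9, fix in advance that the between-arm comparison of falls is adjusted for, or stratified by, falls in the last year (one versus two or more). A Cox model with that covariate, or a stratified log-rank test, can sit beside the Kaplan–Meier curves. State which result is primary, since an adjusted hazard ratio need not equal the unadjusted one.
2. If enrolment has not begun, stratify the random blocks in section 2.8 by the same two levels. If it has begun, leave the list alone and make only the analysis change.
3. In the Discussion, limit the sentence to balanced group sizes.

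The cost is one extra model parameter and, if the blocks are stratified, two lists instead of one. No new data are needed, because prior falls are already established at eligibility.

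Do not also stratify by territory: 2 × 8 strata for 60 people leaves 60 / 16, or about 4 per stratum. Health Unit belongs at most as a random effect in a sensitivity analysis.
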